## 2. Materials and Methods

### 2.1 Study Design and Ethics

This study is a prospective, randomized, double-blind, placebo-controlled, parallel-group clinical trial designed to assess the effect of AA treatment on the therapeutic outcomes and tolerability of MECT in patients with major depressive disorder. The protocol was drafted according to the Standard Protocol Items: Recommendations for Interventional Trials (SPIRIT), and was registered at the Chinese Clinical Trial Registry (Registration No. ChiCTR2500095678) on January 10, 2025. Fig. 1 illustrates the participant flow throughout the study.

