### 2.2 Participants

Potential participants will be screened at the Department of Psychiatry in the First Affiliated Hospital of Chongqing Medical University. Eligible participants will be enrolled after providing written informed consent and may withdraw from the study at any point.

Inclusion Criteria: (1) Diagnostic and Statistical Manual of Mental Disorders, Fifth Edition (DSM-5) diagnosis of major depressive disorder requiring MECT and hospitalization; (2) aged 18–59 years; (3) body mass index (BMI) between 18.5–30 kg/m^2^; (4) physical status (American Society of Anesthesiologists, ASA) I–II, without major comorbidities; (5) willingness of the patients and/or their legal guardian to offer written informed consent.

Exclusion Criteria: (1) comorbid with severe medical and/or surgical diseases, including significant cardiovascular or cerebrovascular diseases, uncontrolled hypertension, elevated intracranial pressure, or the presence of cardiac pacemakers or intracranial implants; (2) co-occurring psychiatric disorders (e.g., schizophrenia); (3) conditions that may interfere with efficacy assessments (e.g., catatonia (diagnosed by experienced psychiatrists according to DSM-5 criteria), cognitive impairment, illiteracy, or intellectual disability); (4) contraindications to anesthesia or MECT (e.g., full stomach, severe pulmonary dysfunction, known allergy to anesthetics); (5) known allergy to ascorbic acid or any contraindications to its administration; (6) history of alcohol or other substance dependence; (7) previous ineffectiveness or serious adverse effects of MECT; (8) pregnancy; (9) participation in another clinical trial within the past year.

Participants will be discontinued from the study if any of the following occur: (1) serious adverse effect necessitating termination of the intervention; (2) request by the patient and/or family to withdraw; (3) clinical circumstances evaluated by the treating psychiatrist that warrant discontinuation of MECT (e.g., remission according to the 24-item Hamilton Depression Rating Scale (HAMD-24) criteria, defined as a score of <10 on two consecutive assessments, occurrence of severe cognitive impairment, intolerable reactions, or no clinical improvement after eight MECT sessions, etc.); (4) violation of trial protocol.

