Secondary outcomes are as follows. The rate of remission of depression after MECT treatment is assessed with the HAMD-24 scale. Remission requires HAMD-24 score <10 after two sequential sessions, and the rate is derived from the number of remitters divided by the total participants per group [44]. For suicidal ideation (SI), defined as a score ≥2 on HAMD-24 item 3, the remission rate represents the proportion of baseline SI-positive patients achieving a score <2 after MECT [45]. Assessment of accompanying psychotic symptoms will be done with the 18-item Brief Psychiatric Rating Scale (BPRS), which uses a 7-point scale per item. The total score (18 to 126) serves as an indicator of severity; higher values indicate worse symptoms [46]. The Montreal Cognitive Assessment (MoCA) serves to rapidly assess cognitive function, providing a total score of 30; better function is indicated by higher scores [47]. Parameters recorded post-stimulation include: 3 Hz spike and wave activity; multiple spike activity; post-seizure suppression; and seizure duration. Based on common practice in MECT trials, a seizure with a duration longer than 25 s is considered indicative of an effective treatment [33,34], and seizure quality on EEG will be assessed with a specific standardized scale. Vital signs (oxygen saturation, heart rate, blood pressure, etc.), and anesthetic indices (duration, dosages of anesthetics) during each MECT treatment will be recorded. Blood samples will be collected to assess potential mechanistic biomarkers including AA, interleukin-1β (IL-1β), IL-6, tumor necrosis factor alpha (TNF-α), and BDNF.

Safety outcomes will be monitored as well, focusing on adverse events (AEs) associated with AA and/or MECT. An AE constitutes any unforeseen medical occurrence after the intervention. Although AA is generally well-tolerated, any newly observed side effects will be recorded, as well as those of MECT, including memory deficits and muscle pain. Participants will be instructed to report any AEs, which will be assessed by a physician and documented. The occurrence of a serious AE will trigger unblinding, administration of necessary treatment, and mandatory reporting to the Institutional Review Board.

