### 2.8 Statistical Analysis

The intention-to-treat (ITT) analysis set in this study will include all randomly assigned participants, regardless of whether they received MECT treatment or completed the follow-up assessments. Analyses will be conducted using SPSS (version 26, IBM Corp., Armonk, NY, USA). Missing outcome or covariate data, including those from participants in the ITT set without post-baseline data, will be handled using multiple imputation, and a mixed model for repeated measures (MMRM) will be used where appropriate. For the primary outcome (the rate of response to MECT), binary logistic regression, with treatment group as the independent variable and pre-specified stratification factors included as covariates, will serve as the primary analytical method, and results will include an adjusted odds ratio (aOR) with a 95% confidence interval. Additionally, potential interaction effects between the stratification factors (age, sex, baseline HAMD-24 score) and the treatment group will be explored within this model for the primary outcome. The Chi-square test will be used as a supplementary analysis. Categorical variables, expressed as counts (percentages), will be compared between groups using the Chi-square test (or the Fisher’s exact test). Continuous variables will be presented as mean (standard deviation) (if normally distributed) or median (interquartile range) (if non-normally distributed), and compared using *t*-test or nonparametric tests (e.g., Mann-Whitney U test), as appropriate. For secondary-outcome analyses, logistic regression will be performed to adjust for potential confounders. For multiple comparisons, the Bonferroni correction will be applied for the secondary and exploratory outcomes. Specifically, the Bonferroni correction will be applied uniformly across all pre-specified secondary outcomes to control the family-wise error rate. We acknowledge that this is a conservative approach, which prioritizes the control of Type I error over statistical power for these outcomes. Given their exploratory feature, between-group differences in blood biomarker levels from baseline to post-treatment will be compared using an analysis of covariance (ANCOVA) adjusted for baseline values, and the Benjamini–Hochberg false discovery rate (FDR) procedure will be applied to correct for multiple testing. Pre-specified subgroup analyses will be conducted based on age (<45 and ≥45 years), sex (male and female), and baseline HAMD-24 score (divided at the median). These analyses will be performed by including an interaction term between the treatment group and the subgroup variable in the primary statistical model (binary logistic regression). Given the exploratory and hypothesis-generating nature of these subgroup analyses, no multiplicity adjustment will be applied to the interaction tests, and the results will be interpreted with caution. Sensitivity analyses will include the per-protocol (PP) analysis and complete-case analysis, an evaluation using alternative missing-data-handling strategies, and re-analyses excluding specific populations (e.g., protocol violators) to assess the robustness of the findings. All hypothesis tests will be two-tailed, and a statistical significance level will be set at* p *< 0.05.

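### Patients whose MECT is stopped for intolerance leave the study as written, so their closing MoCA may be missing because of the harm it measures and be imputed largely from patients who continued

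*Protocol article*

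**What the plan says.** Section 2.1 of the protocol article describes a trial "designed to assess the effect of AA treatment on the therapeutic outcomes and tolerability of MECT in patients with major depressive disorder", so tolerability is part of the stated aim. The Discussion adds the question whether ascorbic acid (AA) can limit or improve adverse effects.

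Section 2.2 opens its list of stopping reasons with "Participants will be discontinued from the study if any of the following occur". Item (1) is a serious adverse effect that ends the intervention. Item (3) covers circumstances in which the psychiatrist ends MECT. Its examples are remission and "occurrence of severe cognitive impairment, intolerable reactions, or no clinical improvement after eight MECT sessions".

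Section 2.6 says of the cognition outcome: "The Montreal Cognitive Assessment (MoCA) serves to rapidly assess cognitive function, providing a total score of 30". Table 1 schedules it twice, at baseline and before discharge. Adverse effects of AA and of MECT are safety outcomes, marked in Table 1 at each MECT and before discharge. The text says that "any newly observed side effects will be recorded, as well as those of MECT, including memory deficits and muscle pain" and that "Participants will be instructed to report any AEs, which will be assessed by a physician and documented".

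Section 2.8 keeps all randomised patients in the intention-to-treat set and states: "Missing outcome or covariate data, including those from participants in the ITT set without post-baseline data, will be handled using multiple imputation". MMRM is to be used where appropriate. Sensitivity analyses are per-protocol, complete-case, exclusion of groups such as protocol violators, and alternative missing-data strategies that are not named.

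**The concern.** Three provisions that are reasonable one at a time work badly together. Severe cognitive impairment ends participation in the study. Cognition is measured once after baseline, at a visit that a patient out of the study may not have. A missing value is then multiply imputed. Read literally, MoCA goes missing because of the harm it is meant to measure.

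Standard multiple imputation assumes that, given the variables in the model, patients with missing values resemble those with observed values. Here they would be expected to be worse. MMRM does not help, because only one post-baseline MoCA is planned and no on-treatment value can carry the decline. The per-protocol and complete-case analyses drop the same patients, so they do not test the assumption.

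The cognition comparison under the tolerability aim is at stake. If AA reduces or increases stops for cognitive harm, that part of its effect could disappear from MoCA. Stopping for intolerance is also not a defined outcome by arm, so no planned comparison would show it directly. A general adverse-effect record does not by itself separate a mild memory complaint from one that ended treatment.

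**Working it through.** **1. The plan's own figure.** Section 2.7 gives 60% against 80% response, two-sided α 0.05, power 85% and 22.5% attrition. With pooled variance:

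n = [1.96·√(2·0.7·0.3) + 1.0364·√(0.24 + 0.16)]² / 0.2² = (1.270 + 0.655)² / 0.04 ≈ 92.7, so 93 per arm.

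93 / (1 − 0.225) = 120 per arm. Both stated figures reproduce. The present point does not depend on them, but 22.5% of 120 is 27 patients per arm, so the plan expects a material amount of missing end data. It does not split this by reason.

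**2. Where a stopped patient's data go.**

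- Adverse effects: recorded at each MECT and before discharge (Table 1). They are kept.
- MoCA: due before discharge only, while section 2.2 has already taken the patient out of the study. The article does not say whether the assessment is still made.
- If it is not made: multiply imputed under section 2.8. The article does not list the predictors.

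**3. Size of the bias if it is not made.** Let m be an arm's MoCA mean as predicted from patients who continued, p the proportion stopped with MoCA missing, and D the points by which stopped patients fall below that prediction.

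- True arm mean: m − p·D.
- Imputed arm mean, with baseline MoCA and arm as predictors: m.
- Part of the AA-minus-placebo difference that is lost: p₀·D₀ − p₁·D₁ (0 = placebo, 1 = AA), which is D·(p₀ − p₁) if D is the same in both arms.

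The documents give no stopping rate and no MoCA mean or SD. All values below are assumptions. Patients who continue are taken as equal between arms.

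| Stopped, placebo / AA | D (points) | True difference lost |
|---|---|---|
| 5% / 2% | 4 | 0.03 × 4 = 0.12 |
| 10% / 5% | 6 | 0.05 × 6 = 0.30 |
| 10% / 3% | 6 | 0.07 × 6 = 0.42 |
| 12% / 4% | 8 | 0.08 × 8 = 0.64 |
| 15% / 5% | 4, 6, 8 | 0.10 × D = 0.4, 0.6, 0.8 |
| 20% / 8% | 10 | 0.12 × 10 = 1.2 |
| equal in both arms | same in both arms | 0 |

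**4. Simulation check.** The set-up was 120 per arm, 2000 runs, and 5 imputations of end MoCA from baseline MoCA and arm. Baseline mean was 26 (SD 2.5), slope 0.6 and residual SD 2, all assumed.

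| Stopped, placebo / AA | D | Full-data difference | After imputation |
|---|---|---|---|
| 10% / 5% | 6 | 0.30 | −0.01 |
| 15% / 5% | 4 | 0.39 | 0.00 |
| 15% / 5% | 6 | 0.60 | 0.00 |
| 15% / 5% | 8 | 0.79 | 0.00 |

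Imputation returns the contrast among patients who continued, here zero, as the formula says.

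**5. What a count of stops could show.** At 120 per arm, two-sided 0.05, pooled z, nothing missing, power is 31% for 10% against 5%, 60% for 10% against 3%, 63% for 12% against 4%, 74% for 15% against 5%, and 77% for 20% against 8%. Such a row is therefore best read as an estimate with its interval.

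**The case against.** A reader might infer that these patients are counted in no outcome and that the tolerability aim loses its decisive cases. The documents do not support that. MECT adverse effects, with memory deficits named, are a scheduled safety outcome at each session and before discharge. Reported events are assessed and documented by a physician, and the patients stay in the intention-to-treat set. This objection stands in full.

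A reader might also take the missing MoCA as certain. It is not. Inclusion requires hospitalisation, and the second MoCA is tied to discharge, not to a number of sessions. Item (3) of section 2.2 speaks of ending MECT and also lists remission. If leaving the study cancelled the closing assessment, patients stopped for remission would have no closing HAMD-24 either, which is hard to square with Table 1. A sensible site might well assess everyone at discharge. What remains is that the list opens by discontinuing participants from the study and that nothing says assessment continues.

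The imputation predictors are not given, and an article may leave them to the analysis plan. Session-level data on adverse effects, seizures and anaesthesia could serve as auxiliary variables, and the unnamed alternative strategies could include a missing-not-at-random analysis. Either could reduce the bias, but neither restores a MoCA that was never taken.

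The zero after imputation follows from the assumptions, and 8 points is not credible for every non-cognitive intolerance. The arithmetic shows a mechanism, not an expected size. Finally, MoCA is one of several Bonferroni-adjusted secondary outcomes. The point does not concern the primary response analysis.

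**Conclusion.** The point holds in a limited form. As written, patients stopped for a serious adverse effect, severe cognitive impairment or intolerable reactions leave the study. Their adverse effects are kept, but their closing MoCA may not be taken, and multiple imputation would then fill it in largely from patients who continued. If the arms differ in such stops, the MoCA comparison is biased toward no difference, by roughly the deficit times the difference in stopping proportions.

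This rests on three conditions: the closing MoCA is in fact not taken, the imputation model carries little information on the decline, and stops or deficits differ between arms. With equal stops and equal deficits the bias is zero. The size cannot be determined from the documents. The combinations tried give 0.12 to 1.2 points, on assumed rates and deficits only.

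It should be corrected although it touches only secondary and safety outcomes. The remedy costs little, and the loss cannot be repaired at the analysis stage.

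**What to change.** - In section 2.2, separate stopping MECT from leaving the study. Only withdrawal of consent should end data collection. The clinical reasons for stopping MECT stay as they are.
- In section 2.6 and Table 1, require MoCA and HAMD-24 when MECT stops, or state that the before-discharge assessment is kept, for every randomised patient who has not withdrawn consent. Use that value as the patient's outcome.
- Add a safety row: MECT stopped for a serious adverse effect, severe cognitive impairment or intolerable reaction, by arm and reason, with the risk difference and 95% confidence interval.
- In section 2.8, name a missing-not-at-random sensitivity analysis for MoCA. Limit any worst-rank rule to patients stopped for cognitive impairment. Applied to all intolerance stops, it would mix non-cognitive reactions with cognition.

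The cost is one table row, built from stopping reasons that a site would normally record, one sensitivity analysis, and a moved or retained MoCA and HAMD-24 for the patients who stop. The small downside is that MoCA timing differs for these patients, so its date should be reported.

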### 2.3 Randomization

We plan to enroll 240 participants. An independent investigator, who is not otherwise involved in the trial, will generate a computer-based randomization sequence. Participants will be randomized using a stratified block randomization method, with stratification based on age, sex, and baseline 24-item Hamilton Depression Rating Scale (HAMD-24) score. A fixed block size of 4 will be used. Subjects will be assigned 1:1 (n = 120 per group) to either the ascorbic acid group (AA Group) or the placebo group (Placebo Group). Concealment of allocation will be ensured until intervention using sequentially numbered, opaque, sealed envelopes. All personnel will be blind to the treatment of the subjects throughout the trial. The research staff responsible for participant enrollment will safeguard the allocation sequence but will have no involvement in the randomization process, clinical interventions, or outcome assessments. All treating clinicians (psychiatrists, anesthesiologists, nurses), outcome assessors, participants, and their families will remain blind to group assignments during the duration of the trial. Emergency unblinding is permitted only for serious adverse events requiring intervention knowledge for clinical management, per the predefined procedure.

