### 2.4 Intervention

Participants will receive an intravenous infusion of AA or the matching placebo (saline) immediately prior to anesthesia induction for each MECT session. This administration is fully synchronized with the MECT procedure, meaning that each intervention (or placebo) dose is given before every electroconvulsive therapy session. Participants in the AA Group will receive 500 mg of AA (2 mL containing 0.5 g; Xinhua Pharmaceutical Co., Ltd., Zibo, Shandong, China),constituted by diluting the solution with normal saline to a final volume of 100 mL. Participants in the Placebo Group will receive 100 mL of normal saline alone. All study solutions will be prepared under aseptic conditions by independent personnel not involved in the trial’s clinical conduct. The final solutions for both groups are visually indistinguishable (clear and colorless liquids) and will be dispensed in identical, tamper-evident, light-proof containers to ensure blinding throughout preparation, handling, and administration.

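### Section 2.3 gives custody of the allocation sequence to the staff who enrol participants, which is inconsistent with its claim that concealment is ensured

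*Protocol article*

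**What the plan says.** All the relevant role assignments are in sections 2.3 and 2.4 of the protocol article.

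- Generation (2.3): "An independent investigator, who is not otherwise involved in the trial, will generate a computer-based randomization sequence".
- Scheme (2.3): permuted blocks "with stratification based on age, sex, and baseline 24-item Hamilton Depression Rating Scale (HAMD-24) score", and "A fixed block size of 4 will be used".
- Concealment (2.3): "Concealment of allocation will be ensured until intervention using sequentially numbered, opaque, sealed envelopes".
- Custody (2.3): "The research staff responsible for participant enrollment will safeguard the allocation sequence but will have no involvement in the randomization process". The sentence goes on to exclude these staff from treatment and from outcome assessment as well.
- Blinding (2.3): "All personnel will be blind to the treatment of the subjects throughout the trial". A later sentence lists the blinded parties as treating clinicians, assessors, participants and families. Enrolment staff are not on that list.
- Preparation (2.4): "All study solutions will be prepared under aseptic conditions by independent personnel", who are outside the clinical conduct of the trial.

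No other custodian of the sequence or of the envelopes is named.

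**The concern.** Allocation concealment protects one step: the decision whether and when a particular patient enters the trial. It requires that whoever takes part in that decision cannot learn the next assignment. The custody sentence places the sequence with exactly those people.

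The entry step leaves room for judgement. Section 2.2 asks staff to decide whether comorbidities are major, whether a condition would interfere with the efficacy ratings, and whether the patient or guardian is willing to consent. The timing of entry is also open. A person with foreknowledge could, even without intent, steer patients with a better outlook towards one arm.

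The primary outcome, treatment response, is the trial's only confirmatory comparison. Groups that differ at entry stay different however well the later care and ratings are blinded. The adjustment in section 2.8 covers only age, sex and baseline HAMD-24, so it would not remove selection on unmeasured prognosis.

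**Working it through.** **1. Does the custody sentence fit the other statements in 2.3?**

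| Statement in 2.3 | Enrolment staff hold a readable list | Enrolment staff hold only sealed envelopes |
|---|---|---|
| Concealment is ensured until intervention | Fails: the next assignment can be read | Rests on the enrolment staff themselves |
| All personnel are blind | Fails for these staff | Can hold, if no envelope is opened early |
| Custodians take no part in randomisation, treatment or assessment | Can hold, but does not protect the entry step | Same |

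The last row matters most. Keeping these staff away from treatment guards against performance bias, and keeping them away from ratings guards against detection bias. Neither guards against selection bias, which arises at enrolment, the step these staff do carry out. Independent generation of the list does not help if the list then goes to them.

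**2. What does the fixed block of 4 add?**

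Inputs: 1:1 allocation (2.7) and blocks of 4 (2.3). Assumption: the guesser knows every earlier allocation in the same stratum and always names the arm that is behind, or guesses at random when the arms are level.

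- Position 1: arms level, so correct with probability 1/2.
- Position 2: two of the three remaining places belong to the other arm, so 2/3.
- Position 3: with probability 1/3 the first two were alike and the assignment is certain; with probability 2/3 the arms are level. Correct: 1/3 × 1 + 2/3 × 1/2 = 2/3.
- Position 4: always certain, so 1.

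Expected correct: 1/2 + 2/3 + 2/3 + 1 = 2.83 of 4 = 70.8% (chance: 50%). Expected number fully determined: 1/3 + 1 = 1.33 of 4 = 33.3%.

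Full enumeration of the blocks gives the same values, and these for other sizes:

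| Fixed block size | Fully determined | Guessed correctly |
|---|---|---|
| 2 | 50.0% | 75.0% |
| 4 | 33.3% | 70.8% |
| 6 | 25.0% | 68.3% |
| 8 | 20.0% | 66.6% |

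**3. Would varying block sizes cure this?**

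This guesser needs only the running imbalance, because every block ends level. Knowing the block size is unnecessary. For sizes 2, 4 and 6, equally likely, the expected correct guesses per block are 2 × 0.750 = 1.50, 4 × 0.708 = 2.83 and 6 × 0.683 = 4.10. The share is (1.50 + 2.83 + 4.10) / (2 + 4 + 6) = 8.43 / 12 = 70.3%, against 70.8% for the fixed block of 4. What undisclosed, varying sizes mainly reduce is the number of assignments known with certainty.

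**4. Is the sample size affected?**

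No. The figures in 2.7 reproduce: 60% against 80%, two-sided 0.05, 85% power and pooled variance give 93 per group, and 93 / (1 − 0.225) = 120.

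**The case against.** The strongest reply is that safeguarding may mean no more than keeping the sealed envelopes intact. Read with the envelope sentence and the blinding sentence, this gives custody without knowledge, and the section is then not strictly contradictory. A condensed article may also leave the details of envelope handling to the full protocol.

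Part of this stands. A reader might infer that enrolment staff know every upcoming assignment. The document does not say that they hold a readable list, so it does not support that inference. But the text says sequence, not envelopes, and the milder reading still leaves all upcoming allocations with the enrolment staff at a single centre. Nor is this a matter of omitted detail: the article assigns the role, and assigns it to the wrong people.

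A reader might also infer that the fixed block of 4 by itself defeats concealment. The document does not support that either. The 70.8% needs earlier allocations in the same stratum to be known. Under 2.4 the solutions look identical and come in identical, tamper-evident containers, and 2.3 keeps clinicians, assessors, participants and families blind. The documented leak is unblinding after a serious adverse event (2.3 and 2.6), which reveals single patients. Stratification scatters these further: with two levels per factor (an assumption, as 2.3 gives no cut-points) there are 2 × 2 × 2 = 8 strata. This part of the objection stands, and the block size is therefore secondary.

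**Conclusion.** The point holds for custody. As written, 2.3 puts the allocation sequence in the hands of the staff whom concealment is meant to restrain, and this is inconsistent with its claims of ensured concealment and complete blinding. On the worse reading assignments can be foreseen; on the milder one concealment depends on the conduct of the enrolment staff. Which reading was meant cannot be settled from the article, so the sentence has to be changed in either case.

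The resulting bias cannot be quantified from the document, because it depends on what these staff can see and whether they act on it. It is a threat to internal validity and does not alter power or the planned 240 participants.

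The fixed, published block of 4 is a minor aggravating factor. Its figures (70.8% guessed correctly, 1.33 of 4 certain) are conditional on earlier allocations in the stratum becoming known.

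**What to change.** Reword 2.3 so that the sequence and the envelopes are held by named personnel with no part in enrolment. The independent preparation personnel in 2.4 are the natural choice, since someone must learn each allocation in order to prepare the solution. State explicitly that they take no part in screening or enrolment, and except them from the statement that all personnel are blind. The sequence generator is less suitable, because 2.3 describes that person as not otherwise involved in the trial.

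Enrolment staff would register consent and stratum data, and only then receive a sequential participant or kit number. If enrolment has begun, document who has actually held the sequence and in what form.

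The cost is a change of wording and of the delegation record. The roles already exist and the sample size is unchanged.

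Optional: use varying block sizes that are not disclosed to site staff. This means regenerating the unused part of the list. It would reduce assignments known with certainty but leave the guess rate at about 70%, so it does not replace the change of custody.
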